## Abstract

**Background:**

Neoantigen-based vaccines show promising therapeutic potential in solid tumors such as melanoma, GBM, NSCLC, and CRC. However, clinical responses remain suboptimal in stage IV patients, due to ineffective T-cell function and high tumor burdens. To overcome these limitations, our study investigates a combination strategy using neoantigen peptide vaccines and precision critical lesion radiotherapy (CLERT), which delivers immunomodulatory doses to key tumor regions synergistically enhance immune activation and inhibit progression in multifocal stage IV patients.

**Materials/Methods:**

This is an open-label, multicenter phase II randomized study. The main objective is to evaluate the anti-tumor efficacy of personalized tumor neoantigen peptide vaccines and assess how different radiation doses synergize with vaccination in treating patients with advanced malignant tumors who have progressed after systemic therapy. Patients are stratified by cancer type and randomized 1:1 to receive either placebo with conventional treatment (including high and low dose radiotherapy) or a personalized neoantigen peptide vaccine alongside conventional treatment (including high and low dose radiotherapy). A one-way crossover design is implemented, permitting patients in the placebo arm to transition to the experimental arm upon progression. Clinical outcomes including progression-free survival and objective response rate are assessed both before and after crossover. Key inclusion criteria are as follows: 1) Patients with advanced or recurrent cancers detected by pathology and imaging, who failed first-line treatments; 2) Patients with projected survival ≥3 months and an ECOG score of 0-2; and 3) Patients with at least one predicted high-quality tumor neoantigen.

**Conclusion:**

This trial introduces an innovative combination strategy of precision radiotherapy and neoantigen vaccine. A notable feature of this study is the incorporation of a randomized control and intra-group crossover design, which is rarely utilized in neoantigen trials. The study is designed to provide critical insight into radiation-immune synergy and the clinical benefit of personalized immunization. Additionally, a basket-trial framework is employed, leveraging shared neoantigens across cancer types to improve efficiency and generalizability. This approach may reduce preparation time and cost, facilitating broader implementation of neoantigen-based immunotherapies. Altogether, this trial design represents a significant step toward translational application of tumor neoantigen vaccines and provides a platform for future combinational immunotherapy strategies.

**Trial registration:**

https://clinicaltrials.gov/study/NCT06314087, identifier: NCT06314087; www.chictr.org.cn, identifier: ChiCTR2300078055. Global Collaborative Oncology Group (GCOG) identifier: GCOG0028.

## Introduction

1

With the advance of tumor immunology, tumor immunotherapy is emerging as “fifth therapeutic pillar” following surgery, radiotherapy, chemotherapy, and targeted therapy (1). Although immune checkpoint blockades (ICBs) targeting PD1 or PD-L1 have been widely utilized across various cancer types, complete responses can only be detected in a fraction of patients, with around 25% overall response rate (2, 3). Especially in advanced-stage patients following conventional first-line and second-line treatments, response rates are relatively low and drug resistance frequently occurred (4). In such cases, personalized and precise treatment approaches, including tumor neoantigens customized for individual patient, are necessary (5). In comparison to traditional tumor-related antigen therapy, this approach offers enhanced specificity, reduced damage to normal tissues, lower risk of autoimmunity, and the ability to target multiple antigens simultaneously (6). This method provides the advantage of activating cytotoxic T cells specifically to eliminate tumor cells (6).

Previous research has demonstrated that neoantigen vaccines can induce neoantigen-specific T cell responses and show promising clinical benefit in certain settings. In 2017, two early-phase clinical studies in advanced melanoma, one led by Ugur Sahin (7) (objective response rate:8/13) and the other by Patrick A. Ott (8) (objective response rate:4/6), reported promising rate of tumor control, particularly in post-surgical patients or those who subsequently received ICBs. Furthermore, neoantigen-based immunotherapies, especially in combination with ICBs, may have potential in other solid tumors, such as gastrointestinal (9), colorectal cancer (10, 11), as well as in a broader range of cancers (12) including non-small cell lung cancer, renal cell carcinoma, urothelial cancer, and triple-negative breast cancer. However, current evidence is limited, as many studies in these cancer types are based on small patient cohorts and lack large-scale clinical validation. For example, a phase 1 trial published in *Nature Medicine* (2025) showed that combining the individualized mRNA vaccine autogene cevumeran with atezolizumab achieved clinical responses in patients unresponsive to immunotherapy (12). In a phase 2 trial conducted by [name] team, the combination of neoantigen-reactive tumor-infiltrating lymphocytes (TILs) and pembrolizumab induced responses in 23.5% of patients with refractory gastrointestinal cancers (9). Tumor neoantigen vaccine, or their combination with ICBs, appear particularly promising in patients after surgical resection (8, 13, 14). A phase 1 study in high-risk renal cell carcinoma patients, reported in Nature (2025), demonstrated a 100% recurrence-free survival rate at 40.2 months post-surgery, supporting their use in achieving near-complete clearance of minimal residual disease (15). However, for patients in advanced stages where surgical resection is not an option, the tumor burden is high and it takes time for neoantigen vaccines to elicit an immune response (16). Therefore, combining late-stage therapies controlling local tumor with neoantigen vaccines is considered the optimal treatment approach.

Radiotherapy is the standard treatment for patients with advance cancer, that can eliminate tumor cell by multiple pathways. In addition to direct tumor killing, research indicates that local radiotherapy can trigger systemic responses in the body, particularly post-treatment, leading to increased release of tumor-associated antigens and damage-associated molecular pattern molecules (DAMPs), ultimately inducing immunity or vaccination *in situ (*
17). Additionally, studies have shown that radiotherapy enhances tumor antigen presentation, boosts the variety of tumor-related antigens in draining lymph nodes, elevates T cell recruitment, and enhances the body’s ability to recognize and combat tumors (18, 19). Palma’s phase 2 SABR-COMET study (20) showed that stereotactic ablative radiotherapy (SABR) for metachronous oligometastatic advanced tumors significantly extended survival (41 *vs*. 26 months) but increased adverse reactions, though quality of life remained unaffected. Similarly, Gomez’s trial (21) on non-small cell lung cancer (NSCLC) with synchronous oligometastatic found that local consolidation radiotherapy greatly improved both survival (41.2 *vs*. 17 months) and progression-free survival (14.2 *vs*. 4.4 months). These clinical studies provide strong evidence supporting the effectiveness of local radiotherapy consolidation in advanced lung cancer. Our recent studies further investigated the dynamic changes in various types of immune cells and related factors during radiotherapy treatment. The data revealed that different radiotherapy doses and techniques have varying effects on both the tumor immune microenvironment (TIME) and the circulating immune system (STIE) (22). It is noteworthy that clinical data from large samples across different cancer types indicate that radiotherapy can lead to lymphopenia, which is associated with poor prognosis. Furthermore, alterations in immune factors like Transforming growth factor-beta (TGF-β) (23–25) and Indoleamine 2, 3-dioxygenase (IDO) (26) before and during radiotherapy are closely linked to tumor control and survival, showcasing the diverse patient responses to radiotherapy. Our previous personalized radiotherapy studies have shown that even under the same radiotherapy dose, different patients or tumors exhibit distinct responses to the same treatment regimen (27). For instance, Positron Emission Tomography-Computed Tomography (PET-CT) scans have revealed variations in tumor regression and normal organ damage among patients, illustrating the heterogeneous tumor response to treatment (28). Additionally, we observed that the volume factor, which refers to the changes in tumor volume during treatment, had significant effect on survival, highlighting how treatment response heterogeneity influences the final treatment outcome (29). By utilizing biological metabolic imaging to guide FDG-PET mid-treatment response and employing adaptive radiotherapy technology (BigART) to tailor treatment for stage III NSCLC patients undergoing concurrent chemotherapy, we have demonstrated that optimizing individual doses, enhancing tumor dose delivery, and protecting normal tissues through BigART can ultimately enhance tumor control and prolong survival (30, 31). Multi-center clinical trials have confirmed the aforementioned findings, and we presented the results of RTOG1106 at the 2020 World Lung Cancer Congress (32). Our study achieved the highest ranking in Phase III trials. Recognizing the variability in individual responses to radiotherapy and the potential for toxic side effects, we propose a novel approach known as critical lesion eliminating radiation therapy (CLERT) for stage IV patients. This method follows isotoxicity planning and adheres to radiation dose limits outlined in the NCCN guidelines for organs at risk (OAR), with a dosage limit set at 80% of the recommended level. By implementing precise and personalized radiotherapy, our aim is to optimize therapeutic outcomes while minimizing damage to both the local and systemic immune microenvironments.

Combining radiotherapy and immunotherapy has the potential to enhance both innate and adaptive immunity, ultimately improving patient survival rates. This suggests a potential of synergetic effect with neoantigen vaccines. The immunomodulatory effects of radiotherapy deponed upon various factors such as dose, fractionation, and timing (33). High-dose radiotherapy (HDRT) with doses exceeding 8Gy (33, 34) enhances tumor recognition by T cells, promoting immunogenic cell death (ICD) (34) and T cell activation (35), but also increases regulatory T cells (Tregs) (36) and myeloid-derived suppressor cells (MDSCs) (37–39). HDRT can trigger systemic anti-tumor immunity and synergizes with immune checkpoint blockade (39). Low-dose radiotherapy (LDRT) with doses below 2Gy (33), though less directly tumoricidal, reshapes the tumor microenvironment, suppresses Tregs, MDSCs and rebalances TH1/TH2 (40), and maximizes immunomodulatory effects (activation of dendritic cells (DCs), T cells, NK cells, and B cells) (41) with lower toxicity, enabling multi-site irradiation (41, 42). Various regimens exist in the clinic, with LDRT paired with HDRT, chemotherapy, or immunotherapy for enhanced tumor control (43). Research on radiotherapy combined with neoantigen vaccines remains limited. A preclinical mouse study in 2020 demonstrated that radiotherapy induced the release of neoantigens, which when combined with neoantigen vaccines, led to the expansion of neoantigen-specific CD4+T cells and CD8+T cells, significantly enhancing the anti-tumor effect (18). While these findings are encouraging, it is important to note that results from mouse models do not always translate directly to humans, particularly in advanced cancer stages. Additionally, a clinical trial evaluating the combination of personalized neoantigen vaccines and radiotherapy has been registered in the United States (NCT02287428), although its results have not yet been published. Collectively, these studies suggest (1) Radiotherapy can upregulate the expression of genes containing immunogenic mutations. This means that radiotherapy can increase the visibility of neoantigens to the immune system; (2) Neoantigen-specific CD8+ T cells preferentially kill irradiated tumor cells. This cytotoxic activity relies on the ability of radiation to upregulate class II MHC molecules as well as the death receptors FAS/CD95 and DR5 on the surface of tumor cells. (3) Combining neoantigen vaccines with radiotherapy and chemotherapy might achieve better therapeutic effects. This is because the combination can help overcome immunosuppression in the tumor microenvironment and optimize neoantigen presentation to the immune system. This provides a theoretical foundation for further exploration of neoantigen vaccine combined with radiotherapy.

To date, there is a lack of literature both domestically and internationally regarding the application of personalized radiotherapy in conjunction with tumor neoantigen peptide vaccines for the precise treatment of advanced tumors. Furthermore, our research team has previously conducted studies on tumor tissue gene mutation sequencing analysis, HLA typing sequencing analysis, and the prediction and identification of tumor neoantigens.

This study aims to enroll patients with advanced tumors who have not responded to standard treatments. The study aligns with the international NCCN Clinical Practice Guidelines (2024.v1) and 2023.V3 versions, as well as recent literature by Ionescu et al (44) and Kuang et al (45). It emphasizes the importance of gene sequencing testing as a standard diagnostic method for advanced stage diseases and recommends that current patients be treated in line with these guidelines. The clinical research process of this personalized tumor neoantigen peptide vaccine combined with radiotherapy: (1) Analyzing individual patient tumor tissue sequencing data, tumor tissue RNA transcriptome sequencing, and control blood sample whole exome sequencing data to assess tumor gene mutation, expression levels, and HLA typing; (2) Neoantigen prediction is a critical step in the development of personalized neoantigen vaccines. However, current prediction algorithms differ in terms of their evaluation of MHC binding affinity, peptide processing, and immunogenicity scoring, which can result in variability in predicted candidates. To improve prediction reliability, we utilized three independent teams with complementary algorithms: the TruNeo^®^ platform (46), the ImmuneMirror (47) algorithm, and a Bayesian-based neoantigen prediction model (48). Each pipeline has unique strengths in modeling antigen processing, MHC binding, and immune response likelihood. We integrated their results to prioritize neoantigen peptides that were commonly predicted by at least two algorithms. Immunogenic neoantigens were defined as those with strong binding affinity to patient-specific HLA alleles, confirmed expression in tumor RNA-seq data, and consistent prediction across multiple algorithms, ensuring higher accuracy and minimizing the risk of selecting non-functional peptides”; (3) Synthesizing tumor neoantigen peptide vaccines for *in vitro* and *in vivo* safety testing; (4) Administering precision radiotherapy followed by the individualized tumor neoantigen peptide vaccine clinical trial to evaluate safety, feasibility, and effectiveness. Subjects will provide informed consent before undergoing this combined precision therapy.

## Study design and methods

2

### Study objectives

2.1

This study uses patients’ individualized tumor neoantigens to prepare peptide drugs targeting neoantigens, and combines them with precision radiotherapy to study the effectiveness and safety of patients who fail to respond to conventional treatments.

#### Primary objectives

2.1.1

The primary objective is to evaluate and explore the anti-tumor activity of personalized tumor neoantigen peptide vaccine combined with radiotherapy in the treatment of patients with advanced malignant tumors with the primary endpoint of progression-free survival.

#### Secondary objectives

2.1.2

The secondary objectives to observe and evaluate the safety of combined peptide vaccines under different radiotherapy doses, and to evaluate the impact of RT dose on the immunogenicity of peptide vaccines on local radiotherapy field response and distant response rate.

#### Exploratory objectives

2.1.3

The exploratory objectives are to explore the temporal changes in patients’ quality of life and bioactive markers (neoantigen-specific T cells, cytokines, ctDNA and TCR clonotype persistence) before, during and after treatment.

### Study design

2.2

The trial is an open-label, multicenter randomized phase II study (**Figure 1**), which includes 2 of the following queues:

**Figure 1 f1:**
[figure not shown]
Flowchart of the study design.

**Control group:** placebo + conventional treatment (including radiotherapy) group,

**Intervention group:** personalized tumor peptide vaccine + conventional treatment (including radiotherapy) group,

Subjects will be stratified according to different cancer types and first, second, and third-line treatment stages based on individual condition assessment, and then randomly enter two cohorts in a 1:1 ratio. In addition, there is a one-way crossover experiment (cross-over design) during the research process. Cross-over to the investigational treatment arm (peptide vaccine plus radiotherapy) will be permitted only for patients in the control group who demonstrate radiologically confirmed disease progression, as assessed by RECIST 1.1 and verified by the investigator. Eligibility for cross-over requires that patients meet predefined safety and clinical criteria, including an ECOG performance status of ≤2, absence of Grade ≥3 adverse events, and adequate hematologic, hepatic, and renal function. The proportion, timing, and reasons for cross-over will be systematically recorded and transparently reported. The intervention group will undergo the second phase of personalized tumor peptide vaccine group plus conventional treatment (including radiotherapy), and the response rate of the two phases will be evaluated before and after crossover. In both cohorts, all subjects received radiotherapy, and radiotherapy doses will be further divided into low and high doses. This design will allow us to answer questions about vaccination efficacy and the impact of various radiation doses.

For patients who want to enroll in neoantigen clinical trials, screening for neoantigens may be recommended. It is necessary to take the patient’s fresh tumor tissue (surgery or biopsy or cerebrospinal fluid, pleural effusion, ascites, etc.), and perform whole-exome and whole- transcriptome sequencing on peripheral blood for further clinical development of individualized targeted treatment plans. At the same time, these test data can be used for personalized tumor neoantigen screening in this study. Peptide vaccine therapy requires an 8-week preparation period for the preparation of the peptide vaccine, during which patients continue to maintain standard treatment.

Patients entering the control group’s conventional treatment (including radiotherapy) group will receive conventional treatment plus radiotherapy. Radiotherapy is divided into low-dose and high-dose (first phase); until disease progression occurs, patients can choose to “cross groups” and receive individual treatment. The second stage of treatment consists of tumor peptide vaccine plus radiotherapy (no harm from treatment in the early stage). Patients entering the intervention group ‘s individualized tumor peptide vaccine + conventional treatment (including radiotherapy) group will complete three precise radiotherapy sessions before initiating vaccination with the peptide vaccine. The peptide vaccine treatment will be carried out one week after the end of radiotherapy. The peptide vaccine treatment will last for 5 months. It is a course of treatment until the treatment discontinuation event specified in the protocol occurs. Subjects will continue to undergo post-treatment safety visits, survival follow-ups and tumor progression follow-ups after finishing treatment.

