### Sample size calculation

2.8

This sample size was approximated based on 20% differences between two groups, at 80% detection power.

Calculation method: The primary purpose of this study is to prove that the vaccine treatment group is more effective than the placebo (standard care), with PFS as the main efficacy evaluation index, the planned enrollment time is 24 months, and all subjects are evenly enrolled in the study. The follow-up time is 12 months. According to previous research, it is assumed that the median PFS of the traditional treatment (the control group) is 4 months, and the median PFS of the vaccine group is 10 months (13). The design of crossover of patients who failed in group 1 to group 2 does not affect the statistical results of PFS of the main study. It is based on the PFS before crossover as the statistical calculation.

The 6th month is selected as the interim analysis time node. Considering 0.1 loss to follow-up, 40 patients need to be recruited, with an average of 20 people in each group (**Table 2**). Through the interim analysis, we can make a preliminary validity judgment on the main purpose of this study to determine whether to continue recruiting more patients.

**Table 2 T2:** Sample size calculation for an interim analysis using log rank tests.

Look	Time	–Sample size–		—————Events—————				—Cum.subject time—	
		Group1	Group2	Group1	% of S.S.	Group2	% of S.S.	Group1	Group2
1	6.0	19.2	19.3	6.2	32.1	3.5	18.0	35.6	41.1
2	12.0	38.3	38.5	17.0	44.5	10.4	27.2	98.0	122.8
3	18.0	57.5	57.7	28.7	50.0	18.6	32.2	166.0	217.3
4	24.0	77.0	77.0	40.7	52.9	27.1	35.2	234.9	316.0
5	30.0	77.0	77.0	46.5	60.5	32.3	41.9	268.2	375.1
6	36.0	77.0	77.0	47.7	61.9	33.9	44.0	274.4	393.7

Considering that this study is aimed at pan-tumor and the results of previous studies are based on small samples of liver cancer, we made 4 hypotheticals median PFS prediction values for statistical analysis. The final median PFS was 4 months in the control group and 8 months in the neoantigen vaccine group. The two groups will be enrolled in a 1:1 ratio, α=0.025 (two-sided), β=0.2, and at least 154 subjects with 77 subjects each group are required and the research power reached 80% (**Table 3**).

**Table 3 T3:** Total sample size calculation.

Power	N1	N2	N	Haz ratio (HR)	Ctrl med surv time (M1)	Trt med surv time (M2)	Accrual pat’n	Accrual time/total time	Ctrl loss	Trt loss	Ctrl to trt	Trt to ctrl	Alpha	Beta

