### Clinical trial design

3.2

Published clinical trials of neoantigen vaccines have predominantly been single-arm studies, limiting the ability to thoroughly analyze the efficacy of the vaccine (6). This clinical trial represents a novel approach with a two-arm, randomized group design, allowing for a more comprehensive evaluation of the effectiveness of neoantigen vaccines without inherent bias. In comparison to single-arm studies, this design offers a more robust evidence-based foundation for the clinical implementation of neoantigen vaccines.

This trial design was informed by previous neoantigen vaccine studies, particularly Ott, et al. (8), *Nature* 2017. While the neoantigen peptide design concept is similar, our study introduces several important differences: we employ a randomized controlled design rather than a single-arm study; incorporate radiotherapy (both low- and high-dose) rather than vaccine monotherapy; and include a one-way crossover arm to further evaluate vaccine efficacy. These improvements are aimed at increasing clinical efficacy and evaluating the synergistic potential of radiotherapy and neoantigen vaccines.

To facilitate the inclusion of patients in the control group for neoantigen vaccine treatment, a crossover program has been implemented. This program enables subjects in the control group with ineffective treatment progress to transition to the vaccine treatment group. Such a clinical trial design not only addresses the need for unbiased efficacy evaluation but also creates new treatment opportunities for a broader patient population. Also, cross-over design needs fewer participants compared to a standard parallel randomized controlled trial (RCT).

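### Outcomes before and after the one-way crossover cannot isolate a vaccine effect, and the crossover saves no patients in this trial

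*Protocol article*

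**What the plan says.** All references are to the protocol article.

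- **Assessment before and after crossover.** Section 2.2 states that "the response rate of the two phases will be evaluated before and after crossover". The abstract (Materials/Methods) names both PFS and objective response rate for the same purpose.
- **Who crosses.** Section 2.2: crossover is "permitted only for patients in the control group who demonstrate radiologically confirmed disease progression". In addition, "Eligibility for cross-over requires that patients meet predefined safety and clinical criteria", covering ECOG status, adverse events and organ function. It is also voluntary: "patients can choose to “cross groups” and receive individual treatment".
- **What they receive.** Control patients have radiotherapy in the first phase. Then: "The second stage of treatment consists of tumor peptide vaccine plus radiotherapy".
- **Purpose claimed.** Section 3.2 lists among the trial's improvements that it will "include a one-way crossover arm to further evaluate vaccine efficacy".
- **Efficiency claimed.** Section 3.2: "cross-over design needs fewer participants compared to a standard parallel randomized controlled trial (RCT").
- **What the sizing uses.** Section 2.8: "It is based on the PFS before crossover as the statistical calculation". Section 2.9 likewise limits the primary PFS analysis to data from before crossover. Table 3 has 0.00 for switching in both directions.

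**The concern.** Two statements about the crossover claim more than the design can deliver.

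The first is that the crossover arm adds evidence on vaccine efficacy. Everyone contributing a second phase was selected on the first-phase outcome, selected again on fitness, and selected a third time by their own choice. At the switch they start the vaccine and a further course of radiotherapy together, at a later point in their disease. The switch goes one way, so no patients take the opposite order and nobody is observed concurrently without the vaccine. A gain in the second phase could come from selection or from repeat radiotherapy. A loss could come from more advanced disease and hide a real effect.

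The second is that a crossover needs fewer patients. That holds for two-sequence crossovers in stable conditions, where each patient serves as their own control. If readers accept it here, they will credit the trial with an efficiency it does not have.

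**Working it through.** **1. Reproducing the stated sample size.** Inputs from section 2.8 and Table 3: medians 4 and 8 months (HR 0.50), alpha 0.025 two-sided, 80% power, uniform accrual over 24 of 36 months, loss 0.10 in each arm, switching 0.00.

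- Schoenfeld events: 4 × (2.241 + 0.842)² / (ln 0.5)² = 79.1, so 80. Freedman: (2.241 + 0.842)² × (1.5/0.5)² = 85.5, so 86. Table 2 has 47.7 + 33.9 = 81.6.
- Probability of an observed event, reading the loss as 10% per month (loss hazard −ln 0.9 = 0.1054), with h the event hazard λ plus the loss hazard: (λ/h) × [1 − (e^(−12h) − e^(−36h))/(24h)]. Control: λ = ln 2/4 = 0.1733, giving 0.619. Vaccine: λ = ln 2/8 = 0.0866, giving 0.442. Table 2 shows 61.9% and 44.0%.
- A two-arm parallel log-rank calculation (Lakatos method) on these inputs gives 152.2 patients, against 153 in Table 3 and 154 in the text. The other three rows give 93.4, 962.3 and 326.6, against 93, 962 and 326.

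So 154 is a plain parallel-group log-rank size. A trial on the same inputs with no crossover needs the same number, and the saving is zero.

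**2. What switching would do if it did enter the PFS comparison.** With assumed control-to-vaccine rates of 5%, 10% and 20% per month, the required size rises to 226, 315 and 553, and power at 154 falls to 62%, 47% and 27%. A one-way switch costs patients. The plan avoids this cost by using pre-crossover PFS.

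**3. Selection on progression: PFS.** Take the plan's 4-month control median as exponential, a vaccine with no effect, a second-phase median also of 4 months (an assumption) and no loss. Among patients who have progressed by month τ, the median first-phase PFS t solves 1 − e^(−λt) = 0.5 × F(τ), with λ = 0.1733.

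| Look | F | Median first-phase PFS (months) | Apparent ratio |
|---|---|---|---|
| τ = 6 months | 0.646 | 2.25 | 4/2.25 = 1.78 |
| τ = 12 months | 0.875 | 3.32 | 4/3.32 = 1.20 |
| τ = 24 months | 0.984 | 3.91 | 4/3.91 = 1.02 |
| Planned end, follow-up uniform on 12–36 months | 1 − (0.125 − 0.002)/(24 × 0.1733) = 0.970 | 3.83 | 4/3.83 = 1.04 |

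Loss would push the ratio up, because late progressors are then missed. A second-phase median below 4 months, which is plausible in later-line disease, would push it down.

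**4. Selection on progression: response rate.** This is an illustration only. Section 3 puts the response rate of radiotherapy or vaccine alone at about 30%. Assume 30% response to each radiotherapy course, a vaccine with no effect, responder median PFS of 6 to 10 months, non-responder median of 2.7 to 3.4 months, and loss of 10% per month. About 61% of controls are then seen to progress, and their first-phase response rate is 19% to 25%. If the second course again gave 30%, response would appear to rise by 5 to 11 points. A lower response in later-line disease would reverse this.

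**The case against.** The strongest reply is that the plan already does most of what is asked. Section 2.2 and the abstract say only that outcomes are assessed before and after crossover. Section 2.9 lists no before/after test, describes the analysis as mainly descriptive, and bases primary PFS on pre-crossover data. Section 3.2 also gives the crossover an access purpose. The proportion, timing and reasons for crossover will be reported, and in-field and distant response are already separate endpoints. The sample-size sentence stands in the Discussion and enters no calculation.

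Much of this stands, and it is why the point is minor. It does not remove the phrase in 3.2 that gives the crossover arm an efficacy role, nor the sentence that contradicts the trial's own sizing.

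Several stronger readings are tempting but not supported:

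- A reader might infer that the repeat radiotherapy is aimed at the progressing lesion. No section says so; section 2.3.1 defines targets as critical lesions, with the final decision by an expert panel. The confounding needs only that vaccine and radiotherapy arrive together.
- A reader might take the claim of unbiased evaluation in 3.2 to describe the before/after contrast. It describes the overall design.
- A reader might take 1.8 as the general size of the bias. On these assumptions it belongs to a month-6 look and nearly vanishes by full follow-up.

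**Conclusion.** Wrong as written, minor severity. The before/after results cannot be attributed to the vaccine, because patients are selected on progression, fitness and choice, radiotherapy is repeated alongside the vaccine, and there is neither a reverse sequence nor a concurrent control. The direction of bias is uncertain. For PFS, selection alone gives an apparent ratio of about 1.8, 1.2 and 1.02 to 1.04 at month 6, month 12 and full follow-up. These figures rest on exponential PFS, an assumed 4-month second-phase median and no loss. The response-rate figure of 5 to 11 points rests wholly on assumed inputs.

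The statement that the crossover needs fewer patients is false for this trial: the saving is 0 of 154.

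None of this touches the randomised pre-crossover PFS comparison or the stated sample size. The switching adjustments in section 2.9 concern overall survival; they neither suffer from this point nor cure it.

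**What to change.** - **Section 2.2:** state that post-crossover response and PFS are descriptive only, measured from the scan that documents progression as the new baseline, and reported with the existing in-field and distant response endpoints. State that vaccine efficacy rests solely on the randomised pre-crossover comparison.
- **Section 3.2:** reword the efficacy purpose of the crossover arm as access to the vaccine plus descriptive activity data, and delete the sentence on needing fewer participants.

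The cost is a few sentences and one supportive efficacy claim given up. Treatment, crossover access, sample size and the primary analysis do not change.
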